#### Blinding

Given the nature of the intervention, this study will not be blinded as both investigators and participants will know who is wearing hearing aids in each 3-month period.

### Measures

#### Screening

All enrolled participants will not be cognitively impaired and will be screened for adequate cognitive functioning using MMSE. Participants scoring 24 or lower on MMSE will not be eligible for participation.

#### Swinburne University Computerized Cognitive Assessment Battery

SUCCAB is a validated computer-based cognitive battery consisting of 8 measures that were developed, based on cognitive and neuroimaging literature, to focus on cognitive domains that were most likely to decline with increasing age [45]. Studies using this battery have shown cognitive changes sensitive to interventions in 5 to 16 weeks [47,48]. The SUCCAB battery uses a simple 5-button interface and has been validated in other studies involving the elderly [49,50]. The 8 measures of cognitive tests assessed by SUCCAB consist of Simple and Choice Reaction Times, Immediate and Delayed Recognition, Congruent and Incongruent Stroop color-words, Spatial Working Memory, and Contextual Memory.

A performance score for each task will be calculated as the ratio of accuracy and reaction time. This approach takes into account variations in accuracy and response time because of speed versus accuracy trade-offs in performance.

#### Hearing Assessments

Participants will undergo the following hearing assessments:

##### Otoscopy and Tympanometry

Following otoscopy, all participants will undergo tympanometry and acoustic reflex testing to assess the status of the middle ear.

##### Pure Tone Audiometry in Each Ear

To understand the degree of hearing impairment and classify participants according to the type of hearing loss, hearing ability will be measured at threshold frequencies 0.5, 1, 2, 3, 4 kHz in both ears. The choice of frequency to be tested corresponds to the amplification range of most modern hearing aids and is consistent with capturing sensitivity at frequencies affected by sensorineural hearing loss and noise-induced damage. Only participants with either mild or moderate symmetric sensorineural hearing loss will be included in the study.

##### Blamey Saunders Speech Perception Test

A Web-based Speech Perception Test (SPT) will be used in addition to the standard audiogram for the purpose of measuring hearing loss. SPT is a monosyllabic word test used to characterize the form and degree of hearing loss [23]. There will be 5 SPT evaluations altogether: SPT will be performed without hearing aids at baseline, after 3 months, and then at 6 months for all participants included in the trial. It will also be performed with hearing aids immediately after participants are fitted with hearing aids for the first time and at the end of 3 months of auditory training while wearing a hearing aid.

#### Paper-Based Questionnaire

Participants will complete a paper-based questionnaire, which will be structured in the following sections:

##### Demographics

Information on a variety of demographic variables will be collected to describe the characteristics of the study sample.

##### Geriatric Depression Scale

GDS is a self-rating screening scale for measuring levels of depressive symptoms in elderly population [51]. The short version of GDS will be used [52]. The GDS has been found to be a reliable and valid measure of depressive symptoms [53] and to be highly correlated with other measures of such symptoms. GDS was designed for older adults. Items are scored dichotomously (respondents answer “Yes” or “Not” to 5 items). Items assess nonsomatic aspects of depression, thus allowing for discrimination between respondents with depressive symptom and those with medical problems. A cut-off GDS score of 7 will be used, with a score greater than 7 indicating the presence of depression. Participants will answer GDS at baseline, after 3 months, and then at 6 months.

##### Social Interaction Measure

The Berkman-Syme Social Network Index [54] will be used to assess participants’ social interaction and connections with families and friends. Participants will answer the Berkman-Syme Social Network Index at baseline, after 3 months, and then at 6 months.

##### Abbreviated Profile of Hearing Aid Benefit

APHAB [55] is a self-assessment inventory that will be answered by each participant to assess hearing satisfaction (with or without hearing aids). Participants will answer APHAB at baseline, after 3 months, and after 6 months. Four scales of the APHAB will be assessed, namely, (1) ease of communication, (2) effects of background noise, (3) effects of reverberation, such as listening to sounds across a large room, and (4) aversiveness, which will look at uncomfortable loudness of background sounds such as traffic and alarm bells.

### Statistical Analysis

The following statistical analyses will be performed:

Baseline comparison of the 2 groups in terms of demographics, cognition, depression, social interaction, hearing loss, and hearing satisfaction by reporting descriptive statistics of each group as randomized, and an effect size of the difference using Cohen's d.Comparison of the 2 groups in terms of changes in cognition, depression, and social interaction from baseline to 3 months and 6 months, using a per protocol approach for the crossover analysis [39] and an intention-to-treat, multilevel model analysis [56]. These methods will be used to estimate any carryover effects [57].Analysis of SPT results with and without hearing aids as a measure of the efficacy of hearing aids and auditory training with and without hearing aids using multilevel models and again allowing for carryover effects.Analysis of the speech tracking rates from the two 12-week programs of speech tracking using a learning model as described by Blamey and Alcantara [25]. This analysis will yield learning and forgetting rates with and without hearing aids. These learning and forgetting rates are valid measures of cognitive processes that are likely to be affected by the use of hearing aids. These data will also be analyzed using multilevel models again allowing for carryover effects.Analysis of the aided and unaided scores from APHAB will be used to assess how the benefit of hearing aids differed between groups and over degree of hearing impairment (mild/moderate hearing loss).

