### Participant Timeline

Participant prescreening and assessment will take place at information sessions that will be held at several independent living aged care facilities located in Melbourne and at Swinburne University of Technology. Independent living aged care facilities with existing relationships with Swinburne University of Technology will be chosen. Participants attending information sessions at Swinburne University will be individuals in the community who have expressed interest in assisting with research projects run by the university, and have therefore provided their contact information to be stored in Swinburne’s Centre for Human Psychopharmacology (CHP) database. After providing informed consent, eligible participants will be randomized into 2 equal groups (A and B) for the study, as described in Figure 1.

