### Sample Size

Allowing for 2.5% significance, 80% power, and a moderate effect size (f=0.25), a power analysis indicated that a repeated measures mixed effects design with 3 repeated measures required a total sample size of 34 participants, split evenly between the 2 groups. This allows for the comparison of changes from baseline to 3 and 6 months for the 2 groups. Except for participants from Swinburne’s CHP database who will need to travel to attend their auditory training sessions at Swinburne University, all other participants will attend their appointments at their facilities. As a result, only a 10% allowance was made for attrition resulting in an overall sample size of 40.

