### Assignment of Interventions

#### Allocation

Groups will be matched in terms of the degree of hearing loss (mild or moderate) with 1 member from each matched pair randomly assigned to *Group A* and the other member of each matched pair assigned to *Group B*. Allocation will be performed using a system of envelopes prepared and opened by the researcher at the time of recruitment.

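### The between-group comparisons are framed as change from baseline, with neither the baseline score nor the matching factor named as a covariate; adjusting for both would sharpen the 3-month comparison

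*Protocol article*

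**What the plan says.** The Statistical Analysis section of the protocol article sets the main analysis as a "Comparison of the 2 groups in terms of changes in cognition, depression, and social interaction from baseline to 3 months and 6 months". Two methods are named: a crossover analysis on the per-protocol set and a multilevel model by intention to treat, both also meant to estimate carryover. No model terms are listed.

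The same framing appears elsewhere. Outcome Measures defines the primary outcome as change in spatial working memory. Sample Size reports that "a repeated measures mixed effects design with 3 repeated measures required a total sample size of 34 participants, split evenly between the 2 groups", and adds: "This allows for the comparison of changes from baseline to 3 and 6 months for the 2 groups". Since there are only three visits (baseline T0, 3 months T1, 6 months T2), that calculation counts T0 as one of the three responses.

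On allocation, the article states: "Groups will be matched in terms of the degree of hearing loss (mild or moderate"), with one member of each pair randomised to each group. In Statistical Analysis, degree of hearing loss is mentioned only for the hearing-aid benefit questionnaire (APHAB), not for cognition, depression or social interaction.

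**The concern.** A change score subtracts the whole of the baseline value. With equal variances at the two visits, the best-fitting slope of follow-up on baseline is the correlation ρ, which is below 1. Subtracting too much adds noise. A multilevel model that takes T0, T1 and T2 as responses and lets the groups have separate T0 means has the same inefficiency: with complete data, its group difference in T0-to-T1 change is the change-score difference.

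The comparison with most to lose is baseline to 3 months. It is one of the two comparisons the article names, and the only one made before anyone has changed treatment, so carryover cannot affect it. Trial Design also lets Group A participants leave after 3 months to buy aids, so data may be most complete at that point. With about 20 per group, precision there is scarce.

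The matching factor is a related point. Pairing on mild or moderate loss makes the groups alike on that factor. The gain in precision is realised only if the analysis accounts for the factor, and only to the extent that it predicts the outcome.

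**Working it through.** **Inputs from the article.** Sample Size gives "Allowing for 2.5% significance, 80% power, and a moderate effect size (f=0.25"), two groups, three measures and N = 34, so 17 per group. It then says "only a 10% allowance was made for attrition resulting in an overall sample size of 40". Participant Timeline confirms equal groups.

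**Input not in the article.** The between-visit correlation ρ is assumed and varied below.

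**Step 1: reproduce N = 34.** For the group-by-time interaction F test, λ = f²·N·m/(1 − ρ), with df = 2 and 2(N − 2), m = 3 and test level 0.025.
- At ρ = 0.5 and N = 34: λ = 0.0625 × 34 × 3 / 0.5 = 12.75, df 2 and 64, power 0.821.
- At N = 32: λ = 12.0, df 2 and 60, power 0.791.

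So 34 is the smallest even total reaching 80% at ρ = 0.5. Other correlations give 46 (0.3), 40 (0.4), 28 (0.6) and 22 (0.7). The value 0.5 is therefore an inference from N = 34, not a stated figure. For attrition, 34/0.9 = 37.8, so 38; the planned 40 covers it.

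**Step 2: variance of the 3-month comparison.** With outcome variance σ² at each visit:
- unadjusted change: 2(1 − ρ)σ²
- follow-up adjusted for baseline: (1 − ρ²)σ²
- proportion saved: 1 − (1 + ρ)/2 = (1 − ρ)/2

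At N = 34, estimating the slope inflates the adjusted variance by about 1 + 1/30, or 3%.

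| ρ (assumed) | Change, σ² | Adjusted, σ² | Saving | Saving after slope cost |
|---|---|---|---|---|
| 0.3 | 1.40 | 0.91 | 35% | 33% |
| 0.5 | 1.00 | 0.75 | 25% | 22% |
| 0.7 | 0.60 | 0.51 | 15% | 12% |
| 0.8 | 0.40 | 0.36 | 10% | 7% |
| 0.9 | 0.20 | 0.19 | 5% | 2% |

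Simulation with 17 per group (20,000 runs) agrees: about 33%, 22% and 12% at ρ = 0.3, 0.5 and 0.7.

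**Step 3: what this means for power (illustration).** Suppose the group differences at T0, T1 and T2 are 0, +d and −d, that is, the aid's effect appears while it is worn and vanishes when it is removed. The interaction effect size is then f = d/√6, so f = 0.25 corresponds to d = 0.25 × 2.449 = 0.61 SD. With 17 per group and ρ = 0.5:
- change score: noncentrality 0.612/√(1.00 × 2/17) = 1.785, df 32
- adjusted: noncentrality 0.612/√(0.75 × 2/17) = 2.06, df 31
- power at two-sided 2.5%: 30% against 40% (38% after the slope cost)
- power at two-sided 5%: 41% against 52%

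At two-sided 2.5%, before the slope cost, power is 22% against 33% at ρ = 0.3 and 49% against 56% at ρ = 0.7. With a smaller assumed difference of 0.5 SD, it is 20% against 27% at ρ = 0.5.

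**Step 4: the crossover contrast.** (T1 − T0) − (T2 − T0) = T1 − T2, so baseline cancels. With equal correlations between all visits, adjustment gains nothing, and in simulation at N = 34 it costs about 3%. With correlations that decay over time (AR(1), ρ 0.3 to 0.7), the theoretical gain is 3–7%, and about 0–4% in simulation.

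**Step 5: the matching factor.** The article gives no association between degree of loss and any outcome, so no saving can be computed. In T1 − T2 a main effect of the factor cancels too.

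**The case against.** The strongest reply is that the article does not list its model terms. Speaking of changes does not exclude baseline adjustment: change modelled with baseline as a covariate gives the same treatment estimate as follow-up modelled with baseline. Covariate lists commonly sit in a statistical analysis plan, which is not shown. This stands in part. A reader might infer that the plan has decided on raw change and has left the matching factor out of the model; the text supports only that neither covariate is named for these outcomes. The point remains because the change framing is stated in three sections, the sample size counts T0 as a response, and degree of loss is named where its use was intended (APHAB).

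A second reply is that the design was chosen for its within-participant comparison, where baseline cancels. This stands fully. A reader might take the 15–35% as a loss across the whole trial; step 4 shows that it is not.

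Third, ρ is assumed. That stands: the saving is small at 0.8–0.9. Nor is adjustment entirely free, as the slope cost shows.

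A reader might also infer bias, because the envelopes are prepared and opened by the researcher in an unblinded study. Under randomisation the change-score comparison is unbiased. Adjustment handles an observed baseline imbalance better than subtraction does, but it does not repair allocation concealment, which is a separate matter.

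**Conclusion.** The point holds as a precision point about the between-group comparisons, chiefly baseline to 3 months. If that comparison is made on unadjusted change, or with T0 as a response and separate group means, its variance is higher than necessary. Adjustment saves 25% at ρ = 0.5 (about 22% after the slope cost), and 15–35% over ρ from 0.7 to 0.3. These figures assume equal variances across visits and a correlation the article does not give. They come from baseline adjustment alone; none can be attached to the matching factor. Even with adjustment the 3-month comparison has low power at the illustrated effect and ρ = 0.5, so this improves it without making it adequate. The stated sample size of 34 is unaffected. The article shows no validity error here, and the change is worth making because both variables are already collected.

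**What to change.** For every between-group comparison, starting with spatial working memory at 3 months, model the follow-up score with the T0 score of the same measure and mild/moderate hearing loss as fixed covariates. Alternatively, fit the multilevel model with one T0 mean common to both groups, plus the hearing-loss stratum. Leave the T1-versus-T2 crossover contrast without baseline adjustment.

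The cost is two degrees of freedom and a sentence of analysis text; no extra visit, measurement or participant is needed. The Results section reports that data analysis is under way, and the study is not blinded. The model should therefore be specified and dated before group comparisons are examined. If they have already been seen, the adjusted analysis should be labelled post hoc and reported beside the one planned.

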## Abstract

**Background:**

Sensorineural hearing loss is the most common sensory deficit among older adults. Some of the psychosocial consequences of this condition include difficulty in understanding speech, depression, and social isolation. Studies have shown that older adults with hearing loss show some age-related cognitive decline. Hearing aids have been proven as successful interventions to alleviate sensorineural hearing loss. In addition to hearing aid use, the positive effects of auditory training—formal listening activities designed to optimize speech perception—are now being documented among adults with hearing loss who use hearing aids, especially new hearing aid users. Auditory training has also been shown to produce prolonged cognitive performance improvements. However, there is still little evidence to support the benefits of simultaneous hearing aid use and individualized face-to-face auditory training on cognitive performance in adults with hearing loss.

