**Methods:**

This is a crossover trial targeting 40 men and women between 50 and 90 years of age with either mild or moderate symmetric sensorineural hearing loss. Consented, willing participants will be recruited from either an independent living accommodation or via a community database to undergo a 6-month intensive face-to-face auditory training program (active control). Participants will be assigned in random order to receive hearing aid (intervention) for either the first 3 or last 3 months of the 6-month auditory training program. Each participant will be tested at baseline, 3, and 6 months using a neuropsychological battery of computer-based cognitive assessments, together with a depression symptom instrument and a social interaction measure. The primary outcome will be cognitive performance with regard to spatial working memory. Secondary outcome measures include other cognition performance measures, depressive symptoms, social interaction, and hearing satisfaction.

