## Methods

### Trial Design

This study has a randomized crossover trial design. It attained ethics approval on July 22, 2016 (Swinburne’s Human Research Ethics Committee protocol number SHR Project 2016/159).

All participants will undergo an individualized face-to-face auditory training program for a period of 6 months and will be randomly allocated to one of the following groups:

Participants who will be fitted with hearing aids only for the first 3 months of the auditory training program—*Group A.*Participants who will be fitted with hearing aids only for the last 3 months of the auditory training program—*Group B.*

Participants will be tested at baseline, and at 3 and 6 months in terms of cognition, depressive symptoms, social interaction, and hearing satisfaction.

A crossover design is chosen to allow each participant to serve as their own control [39]. Group A participants will have the option to withdraw from the study after 3 months if they decide to purchase hearing aids immediately. Similarly, group B participants will also have the option of withdrawing from the study at any time. As all participants will receive auditory training for the entire duration of the study to address their hearing loss, participants will benefit from the study even when the hearing aid intervention is not in place.

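### With no washout, a crossover estimate without a carryover term is off by half of any aid-specific carryover, and the planned carryover estimate is too imprecise to rule that out

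*Protocol article*

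**What the plan says.** All references are to the protocol article.

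- **Period structure.** The Abstract (Methods) has participants "receive hearing aid (intervention) for either the first 3 or last 3 months of the 6-month auditory training program". Trial Design describes the same two back-to-back periods, with training running through both and testing only at baseline, 3 and 6 months. No gap and no second baseline is described.
- **Reason for the design.** Trial Design: "A crossover design is chosen to allow each participant to serve as their own control".
- **Analysis.** Statistical Analysis compares the groups on change from baseline to 3 and to 6 months, by a per-protocol crossover analysis and an intention-to-treat multilevel model. It adds: "These methods will be used to estimate any carryover effects". It does not say what follows from that estimate.
- **Sample size.** 2.5% significance, 80% power and f = 0.25 for "a repeated measures mixed effects design with 3 repeated measures", which "required a total sample size of 34 participants, split evenly between the 2 groups"; then "only a 10% allowance was made for attrition resulting in an overall sample size of 40". Nothing is allowed for carryover or for estimating it.
- **Limitations.** The Discussion does not mention carryover.

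**The concern.** Group A goes straight from aids plus training to training alone. If part of what was gained while aided is still present at 6 months, Group A's second period is not a clean control period. The within-person contrast then subtracts some of the benefit from itself. The article gives some reason to expect this: its Background says new aid users gain more from training, and its Statistical Analysis expects aids to affect learning and forgetting rates.

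In a two-sequence, two-period layout, carryover is estimated between participants, so it lacks the precision that motivated the crossover. The stake is interpretation. A small crossover estimate could mean no benefit or lasting benefit, and an imprecise carryover estimate could not tell the two apart.

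**Working it through.** **Reproducing the sample size.** For the group-by-time test with k = 2 groups, m = 3 measures, f = 0.25 and alpha = 0.025, with assumed correlation rho = 0.5 and sphericity (neither is stated), the noncentrality is f²·N·m/(1 − rho).
- N = 34: 0.0625 × 34 × 3/0.5 = 12.75, with 2 and 64 df; power 82.1%.
- N = 32: power 79.1%.

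So 34 is the smallest even N reaching 80%, and the stated figure reproduces. Inflation for dropout gives 34/0.9 = 37.8, or 38, against 40 stated.

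**Effect size implied by f.** For a clean crossover pattern the A − B differences at 0, 3 and 6 months are 0, tau and −tau (SD units). Then f² = tau²/6, so tau = 0.25 × √6 = 0.61 SD.

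**Bias.** With a residual lambda in Group A at 6 months, the A − B difference is tau at 3 months and lambda − tau at 6 months. Period effects, including persistence of training that both groups receive, cancel.

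E[crossover estimate] = ½[tau − (lambda − tau)] = tau − lambda/2.

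Simulation (20,000 trials, tau = 0.50) agrees:

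| lambda | simulated mean | tau − lambda/2 |
|---|---|---|
| 0 | 0.499 | 0.500 |
| 0.25 | 0.376 | 0.375 |
| 0.50 | 0.251 | 0.250 |
| −0.25 | 0.625 | 0.625 |

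**Standard errors** (SD = 1, compound symmetry, n = 17 per group):
- Crossover: ½√[2(1 − rho)·2/n]
- Carryover, the group difference in the sum of the two periods, adjusted for baseline: √[(2(1 + rho) − 4rho²)·2/n]
- 3-month contrast, adjusted for baseline: √[(1 − rho²)·2/n]
- 3-month contrast, change scores: √[2(1 − rho)·2/n]

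At rho = 0.5 these are 0.171, √(2 × 2/17) = 0.485, √(0.75 × 2/17) = 0.297 and √(2/17) = 0.343.

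**Power at tau = 0.61, N = 34** (noncentral t, two-sided):

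| rho | SE of lambda | Power to detect lambda = 0.61, 5% level | Crossover power at 2.5%, lambda = 0 | Same, full persistence |
|---|---|---|---|---|
| 0.3 | 0.51 | 21% | 74% | 21% |
| 0.5 | 0.485 | 23% | 88% | 30% |
| 0.7 | 0.41 | 30% | 98% | 49% |
| 0.9 | 0.26 | 64% | about 100% | 94% |

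At full persistence the expected crossover estimate is 0.61/2 = 0.31 SD at every correlation. At rho = 0.5 the 95% interval for lambda is about ±0.99 SD. With all 40 completing, power to detect full persistence at the 5% level is still only 27% at rho = 0.5 and 71% at rho = 0.9.

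**What a carryover term costs.** It removes the bias, but tau then rests on the 3-month between-group contrast. At rho = 0.5 and 2.5% significance that contrast has about 40% power (0.61/0.297), against 88% for the crossover estimate with no carryover and 63% with half persistence.

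**The case against.** **The carryover-free comparison is already planned.** This stands. Sample Size and Statistical Analysis both include change from baseline to 3 months. What is left is baseline adjustment and how that result is set beside the crossover estimate.

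**The bias belongs to one estimator.** This also stands. A multilevel model with a carryover term is not biased by lambda/2, and later items in Statistical Analysis speak of allowing for carryover. The article does not say that its headline estimate omits the term. The point is therefore conditional on an estimate that does.

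**Stronger readings that a reader might infer, and that the article does not support:**
- *That carryover is established, from the statement "Auditory training has also been shown to produce prolonged cognitive performance improvements".* That sentence concerns training, which both groups receive throughout, so its persistence is a period effect and cancels. Only an aid-specific residual matters. Group A's 6-month test comes 3 months after the aided period ends, and the article gives no figure for what remains by then.
- *That the bias is always toward zero.* This needs a residual in the direction of benefit. Worsening after the aids are removed would inflate the estimate.
- *That a carryover test will select the analysis.* Such a two-stage rule inflates type I error: with a 10% carryover test, simulation gave about 7.6% to 7.8% at nominal 5%. But the article speaks of estimating carryover, not of testing and then choosing.
- *That the 3-month contrast should decide whenever the two results disagree.* At rho = 0.5 it beats the crossover for power only near full persistence (about 40% against 30%), and an undefined disagreement rule would itself be data-dependent.

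**Conclusion.** The point holds in a conditional form. A crossover estimate without a carryover term has expectation tau − lambda/2; that is algebra and needs no assumed input. With 34 completers, the planned carryover estimate cannot rule out an important carryover at any correlation from 0.3 to 0.9: its power against full persistence never reaches 80%. The possible loss of crossover power is large at low and moderate correlation but small at 0.9 (about 100% to 94%), although the estimate is still halved there.

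These sizes rest on assumptions the article does not state: the correlation, compound symmetry, and tau = 0.61 SD derived from f = 0.25. The size and sign of lambda are unknown. This should be fixed, but it does not invalidate the trial, because an unaffected comparison is already among those planned.

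**What to change.** 1. Analyse the planned 3-month comparison of Group A with Group B adjusted for baseline, not as change scores (SE 0.297 against 0.343 SD at correlation 0.5), and always report it beside the crossover estimate.
2. Label the crossover estimate as valid only if aid-specific carryover is zero. Show the estimate plus lambda/2 over a stated range of lambda that includes both signs, for example from minus to plus the 3-month effect.
3. State that the carryover estimate will not be used to choose the analysis. This is a precaution, since the article states no such rule.

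The cost is wording and one extra model on data already scheduled for collection. Recruitment is complete and analysis is under way according to the Results section, so the wording should be fixed, and dated, before results are reported. The downside is precision: about 40% power for the 3-month contrast at correlation 0.5 and 2.5% significance. It should accompany the crossover result and not displace it.
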